People with OUD frequently encounter the healthcare system through EDs, primary care clinics, substance use treatment centers, and mental health clinics [17, 18]. Approximately one in every 80 ED visits may be due to opioid-related health issues [19]. The 3-year prevalence of OUD among primary care patients was 0.7–1.4% across seven US health systems between 2014 and 2019 [20, 21]. Approximately one-fifth of people with OUD may also seek out treatment at substance use treatment centers [22, 23]. A significant portion, nearly 60%, of those with OUD also suffer from mild to severe mental illnesses [24]. People with OUD could benefit from an integrated healthcare approach due to their multifaceted health needs, including OUD treatment, mental health care, and HIV prevention; however, the reality is that the healthcare system is fragmented—services like MOUD, mental health services, and HIV prevention care are often delivered across different settings. This disconnection leads to missed opportunities for early intervention and makes it challenging for patients with OUD and/or mental illnesses to remain engaged in PrEP care if they are not concurrently receiving treatment [25, 26].

Rhode Island presents a unique opportunity to address these barriers in HIV prevention among people with OUD through the innovative use of population-level administrative data. The state’s All-Payer Claims Database (APCD), coupled with the State Emergency Department Database (SEDD), enables a comprehensive assessment of insured and uninsured individuals across diverse clinical settings, which could provide important insights into real-world healthcare engagement and service utilization, and offers a foundation for designing and implementing scalable, data-driven interventions.

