#### Data sources

We will use two primary data sources to capture insured and uninsured individuals in RI:Rhode Island (RI) All-Payer Claims Database (APCD) includes longitudinal medical and pharmacy claims, participant demographics and enrollment information, and provider characteristics data from private insurers, Medicare, and Medicaid (Table 1). APCD data are updated monthly and reflect over 90% of the insured population in RI (based on our preliminary analysis). We will use APCD data between 2012 and 2022 to evaluate trends over time.Rhode Island State Emergency Department Database (SEDD): Captures encounter-level data for ED visits, including those involving uninsured individuals (estimated 5.0% of RI population, based on 2022 data) [48]. While SEDD lacks unique patient identifiers and pharmacy/provider details, it complements APCD by providing a more complete picture of ED utilization among patients who may be excluded from claims-based analyses. Because SEDD does not allow for longitudinal tracking of individuals across visits, these data will be used to characterize encounter-level trends among the uninsured population. APCD and SEDD will not be linked at the individual level; however, each will be analyzed separately but interpreted together to capture utilization across the full population of people with OUD.

**Table 1 Tab1:** Data variables for statistical analysis in Aim 1

Demographic data	Medical care information	Provider information
Age Sex ZIP Code City Insurance information Relationship to health policyholder Internal unique identifier	Date of service Type of service Location of service Date prescription(s) filled ICD-9/10 diagnostic codes National Drug Code Prescription refill indicator Pharmacy ID Inpatient and outpatient claims Mental health claims	Practice Attending provider name Prescribing provider name Type Primary care indicator Specialty Address ZIP Code City Pharmacy ID

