#### Study population

The study population will consist of people who are: 18 years of age or older, residing in Rhode Island during health insurance enrollment, and presented evidence of OUD (see OUD criteria below), between 2012 and 2022. To ensure robustness of findings, we will include only individuals who had 6 months of continuous health insurance coverage after their first OUD-related claim within a calendar year. People with OUD will be identified in APCD using one or more of the following:International Classification of Diseases (ICD-9/10) diagnosis codes for OUD, encompassing diagnostic codes for opioid use, opioid abuse, and opioid dependence.Healthcare Common Procedure Coding System (HCPCS) and Current Procedural Terminology (CPT) codes for OUD-related services, including OUD treatment administration (e.g., injection and oral medication administration).National Drug Codes (NDCs) for MOUD, including various forms (e.g., injection and medication), dosages, strengths, and formulations (e.g., branded and generic) of methadone, buprenorphine, and naltrexone.

The study cohort will include individuals with at least one qualifying encounter or prescription during the study period. A supplemental table (Table S1) will provide the complete list of codes used for cohort identification.

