#### Outcome measures

We will assess healthcare utilization across four types of care settings, including ED, primary care, substance use treatment center, and mental health service facility (Fig. 1).ED visits will be identified in APCD using HCPCS (99,281–99,285) and revenue codes (0450–0459, 0981). Uninsured ED visits will be identified in SEDD using OUD and MOUD diagnosis codes. Given the lack of unique identifiers in SEDD, each record represents a single encounter.Primary care visits will be identified using CPT codes for outpatient visits (9201–99215, 99,381–99,397), HCPCS code T1015, and provider specialty codes (01, 08, 11, 19, 31, 38, 50, 84, 97) indicating primary care (e.g., internal medicine, family medicine, nurse practitioners, physician assistants).Substance use treatment visits will be identified via CPT codes for substance use services (e.g., H0015, H0018, H0020), including MOUD-related services. Claims will be restricted to facilities verified as SAMHSA-regulated Opioid Treatment Programs (OTPs) in Rhode Island. We recognize that office-based MOUD services are increasingly provided in primary care and other outpatient settings; however, these visits will be captured under the primary care setting definition.Mental health service visits will be identified using CPT codes (90,791–90853, 99,404) and provider taxonomy for psychiatry, psychology, and behavioral health providers.

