### Aim 3 – Simulation modeling via agent-based modeling

#### Study design

The objective of Aim 3 is to develop and apply an agent-based model (ABM) to simulate HIV transmission, healthcare engagement, and the effect(s) of hypothetical implementation strategies on key health outcomes among people with OUD in Rhode Island. The model will project outcomes over 5- and 10-year horizons, assessing the potential reach and effectiveness of tailored implementation approaches, identified in Aim 2, prior to real-world piloting.

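### Aim 1 sees only people with a recorded OUD or MOUD code, yet its care-use rates feed a model of all people with OUD in Rhode Island, so the reach of clinic-based strategies is likely overstated

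*Protocol article*

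**What the plan says.** **Who enters Aim 1.** The Study population section of the protocol article identifies people with OUD in the claims database by a diagnosis code, an OUD service code or a MOUD drug code: "The study cohort will include individuals with at least one qualifying encounter or prescription during the study period". It then narrows the cohort further: "we will include only individuals who had 6 months of continuous health insurance coverage after their first OUD-related claim within a calendar year". Uninsured people enter only as coded emergency encounters (Outcome measures): "Uninsured ED visits will be identified in SEDD using OUD and MOUD diagnosis codes".

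**What Aim 1 is said to cover.** The Data sources section says of the claims and emergency department databases that "each will be analyzed separately but interpreted together to capture utilization across the full population of people with OUD".

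**What the model represents.** The Aim 3 Study design section gives the model's task as follows: "simulate HIV transmission, healthcare engagement, and the effect(s) of hypothetical implementation strategies on key health outcomes among people with OUD in Rhode Island". Likewise, the Model framework section describes a virtual society of Rhode Islanders with OUD. Neither restricts agents to people who are diagnosed or in care.

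**Where the model's care-use inputs come from.**
- Model input names Aim 1 as the administrative source, with care-use patterns as its example. It draws agents' starting traits, care use and MOUD status among them, from Aim 1 and the literature.
- Outcome definition sets the status-quo base model from Aim 1.
- Model calibration and validation lists emergency department use from Aim 1 as a calibration target, alongside HIV incidence.

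**What is acknowledged.** The Limitations section names uninsured patients seen outside emergency departments. It does not mention insured people whose OUD is never coded.

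**The concern.** The cohort is selected on the thing it is used to measure. Over the study period every claims-cohort member has at least one coded contact or prescription by construction, so the cohort cannot show how often people with OUD in general have contact with care. The full-population statement in Data sources cannot hold under the entry rule in Study population.

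This matters because every strategy to be simulated is delivered in a care setting. How many agents a strategy can reach depends on their probability of contact. If agents who represent uncoded people receive the contact and MOUD probabilities of coded people, the model treats them as more reachable than the data can support. The Outcome definition section says the outputs will guide the choice of strategy package for real-world use, and the Discussion presents the final strategy as validated and ready for implementation.

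**Working it through.** The article gives no cohort size, reach figure or coded share, so there is no stated figure to reproduce. The check uses a simple mixture.

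**Inputs**
- u: the care-use rate seen in the Aim 1 cohort (any value; it cancels).
- f: the share of people with OUD who carry a qualifying code. Not given; assumed range 0.9 to 0.3.
- r: care use of uncoded people relative to coded people. Not given; assumed range 0 to 1, with 1.25 as a counter-case.

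**Formula.** Rate in all people with OUD = f·u + (1−f)·r·u. If u is applied to every agent, the overstatement factor is u divided by that rate, which is 1/(f + (1−f)·r).

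**MOUD and OUD-specific services.** These codes are themselves entry criteria. An insured person with no qualifying code therefore has zero recorded use by definition, so r = 0 and the factor is 1/f.

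**Emergency, primary care and mental health visits.** People can use these services without an OUD code, so r is unknown.

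| f | r = 0 | r = 0.5 | r = 1 |
|---|---|---|---|
| 0.9 | 1/0.90 = 1.11 | 1/0.95 = 1.05 | 1.00 |
| 0.7 | 1/0.70 = 1.43 | 1/0.85 = 1.18 | 1.00 |
| 0.5 | 1/0.50 = 2.00 | 1/0.75 = 1.33 | 1.00 |
| 0.3 | 1/0.30 = 3.33 | 1/0.65 = 1.54 | 1.00 |

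Counter-case, uncoded people using more care: f = 0.5, r = 1.25 gives 1/(0.5 + 0.625) = 0.89, an understatement.

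**Insurance cover is a separate gap.** The claims data "reflect over 90% of the insured population in RI (based on our preliminary analysis", and Data sources puts the uninsured at 5.0% of the population. Cover is therefore about 0.95 × 0.90 = 85.5%, and at most 95%, of the general population before any OUD code is required. High insurance cover says nothing about f.

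**Do the planned checks repair it?**
- *Calibration.* The emergency department target comes from the same selected data, so matching it reproduces the selection. Matching HIV incidence does not show how many agents are in care.
- *Sensitivity analysis.* Each parameter is to be varied one at a time and the most influential ones jointly. That can move care-seeking probabilities, but no out-of-care group or range is stated. Shifting one common probability is not the same as having a subgroup with little contact that still belongs to the transmission network.

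**The case against.** The strongest reply is that the article never says Aim 1 rates will be applied unadjusted to every agent. Model input lists three sources and gives care-use patterns only as an example. Starting traits may also draw on the literature, care-seeking probability is a patient-level parameter in Table 2, and values and assumptions are left to a parameter repository. An article need not describe every stratum. The section on the current study also frames the aim as integration into settings where people with OUD already seek care, for which an in-care cohort is a relevant source. This makes the size of the problem conditional. It does not remove the full-population claim, the Aim 1 status quo, the Aim 1 calibration target or the gap in the limitations.

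Several stronger readings are tempting but not supported:
- **That contact is overstated in all four settings.** It follows by definition only for MOUD and OUD-specific services. Elsewhere it requires uncoded people to use less care, which is likely but not shown.
- **That infections averted are inflated.** The comparison is with a status quo built from the same cohort. If baseline MOUD or PrEP coverage is set too high, there is less room for improvement, which pulls the other way.
- **That a background figure can serve as a check.** The Background says "Approximately one-fifth of people with OUD may also seek out treatment at substance use treatment centers", but that concerns treatment centers generally. Outcome measures restricts this setting to verified opioid treatment programs in the state and counts office-based MOUD under primary care. The two are not comparable.
- **That the qualifying visit is counted as utilization.** The article does not say either way.
- **That people out of care are at higher HIV risk.** Nothing in the article establishes this.

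**Conclusion.** The point holds. The observed population is narrower than the population claimed for Aim 1 and the one described for the model, and nothing in the article bridges the two.

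The size is conditional on Aim 1 rates being applied to all agents and on values the article does not supply. For MOUD and OUD-specific services the factor is 1/f: 1.11 to 3.33 for an assumed f of 0.9 to 0.3. This concerns recorded use; any treatment paid for outside the claims data would make the true factor smaller. For emergency, primary care and mental health contact it is 1.05 to 1.54 over the same range of f at an assumed r of 0.5, and 1.00 at r = 1. The six-month coverage rule probably selects further towards engaged people and is not in these figures.

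The reach of clinic-based strategies is therefore likely overstated. The net direction of bias in infections averted, and so in the number needed to treat, is undetermined. The change should be made, but this does not invalidate the study.

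**What to change.** Choose one of two routes and state it.

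1. **Widen the model.** Add an uncoded, out-of-care OUD stratum to the ABM. Size it as an external range for total OUD in the state minus the Aim 1 cohort. Give it lower contact probabilities and zero or low MOUD, and apply Aim 1 rates only to the coded stratum. Report cases averted and the number needed to treat over stated ranges of f and r.
2. **Narrow the claim.** Restrict the ABM and its conclusions to people with a recorded OUD claim or encounter.

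Under either route, replace the full-population statement in Data sources with wording limited to people with recorded OUD, and add insured people with uncoded OUD to the Limitations section.

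The cost of the first route is one extra agent stratum and a sensitivity range, and projected reach may look less favourable. The second needs no new stratum but gives up statements about all people with OUD in Rhode Island.

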**Fig. 1 Fig1:**
[figure not shown]
Overview of three aims in our study

In particular, we will assess receipt of HIV prevention services, including HIV testing and PrEP, as well as MOUD. We will use CPT codes (86,689, 86,701–86703, 87,534–87,536, 87,390) and HCPCS codes (G0432–G0435) to identify claims for HIV testing. PrEP use will be defined as having a prescription for a 30-day or longer supply of tenofovir/emtricitabine or tenofovir alafenamide/emtricitabine, without a concurrent diagnosis of HIV or hepatitis B virus. MOUD receipt will use the definitions stated above, based on NDC and procedure codes. All utilization outcomes will be summarized and stratified by care setting and insurance type where applicable. We will also explore temporal trends across the study period.

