**Fig. 2 Fig2:**
[figure not shown]
Flowchart of retrospective data analysis in Aim 1

In descriptive analysis, we will summarize annual frequencies and rates of healthcare utilization and HIV prevention service uptake by setting and insurance status. Results will be stratified by age group, gender, race/ethnicity, and geographic region. Statistical tests (e.g., Chi-square, t-test, and ANOVA) and trend analyses will be used to examine differences in service utilization across years and subgroups.

In regression modeling, we will fit multivariable logistic regression models to identify individual- and area-level factors that are associated with receipt of HIV testing, PrEP uptake and retention, and MOUD initiation and retention (defined as continuous MOUD coverage for 180 days, permitting gaps no longer than 7 days) [49]. Covariates will include demographic characteristics (age, gender, race/ethnicity), insurance type, healthcare setting, and SDH indicators (e.g., housing instability, incarceration). Area-level variables from the U.S. Census Bureau (i.e., American Community Survey) will be linked to each individual via zip codes. If data structure allows, we will implement multilevel models to account for clustering at the geographic level. We will report adjusted odds ratios (aORs) with 95% confidence intervals. We will conduct several sensitivity analyses with alternate definitions of PrEP use and retention (e.g., 60-days of supply, and allowing for various lengths of gaps between refills). All analyses will be conducted using SAS 9.4. Statistical significance will be assessed at the *p* < 0.05 level unless otherwise specified.

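### The codes that score MOUD receipt also admit people to the Aim 1 OUD cohort, so some members have the outcome by construction

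*Protocol article*

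**What the plan says.** The Study population section of Aim 1 lists three routes into the claims cohort: diagnosis codes, procedure codes for OUD-related services (among them the administration of treatment), and national drug codes for MOUD. Any one is enough: "People with OUD will be identified in APCD using one or more of the following". One instance is enough too: "The study cohort will include individuals with at least one qualifying encounter or prescription during the study period". The drug route covers "formulations (e.g., branded and generic) of methadone, buprenorphine, and naltrexone", and the text attaches no diagnosis requirement to it.

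The Outcome measures section then scores the outcome from those codes: "MOUD receipt will use the definitions stated above, based on NDC and procedure codes". The same section defines one of the four care settings partly by the treatment: "Substance use treatment visits will be identified via CPT codes for substance use services (e.g., H0015, H0018, H0020), including MOUD-related services". That setting is restricted to verified opioid treatment programs (OTPs), and office-based MOUD is counted under primary care.

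The Aim 1 Analysis plan fits logistic models for factors "associated with receipt of HIV testing, PrEP uptake and retention, and MOUD initiation and retention", with healthcare setting among the covariates. Retention has its own definition: 180 days of continuous cover with gaps of at most 7 days. The sensitivity analyses named there vary only the definitions of PrEP use and retention. In Aim 3, Outcome definition, the status-quo model takes its service levels from Aim 1.

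**The concern.** An uptake proportion is informative when a person can enter the denominator whether or not they have the event counted in the numerator. Here one route in is the event itself. People who enter only by a MOUD code add equally to numerator and denominator, so they pull uptake towards 100% whatever happens among the others. Two further consequences follow from the same rule.

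- A single drug code with no diagnosis can admit someone who does not have OUD, because the rule has no condition on indication.
- In the MOUD initiation model, a person can be classed in the OTP setting because of a MOUD service. Part of that covariate is then the outcome.

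MOUD uptake and its gaps are main Aim 1 results. They are presented at the first stakeholder panel in Aim 2, and they set the baseline of the agent-based model. If baseline MOUD uptake is too high, simulated strategies have less room to raise it, which could affect cases averted, number needed to treat and the comparison of settings.

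**Working it through.** The article states no MOUD uptake rate and no breakdown by entry route, so there is no figure to reproduce. The overlap is read from the text, and its size is shown over assumed ranges.

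**Entry and outcome side by side**

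| Entry route | Also scores MOUD receipt? |
|---|---|
| OUD diagnosis code | No |
| Procedure code, treatment administration | Yes |
| Procedure code, other OUD-related service | No |
| MOUD drug code | Yes |

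**Uptake.** Let f be the share of the cohort that enters only by a MOUD code, and p the MOUD receipt in the rest, treated here as diagnosis-identified. Both are assumptions.

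Cohort uptake = f × 1 + (1 − f) × p = p + f(1 − p), so the excess over p is f(1 − p). It is positive whenever f > 0 and p < 1.

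| p | f = 5% | f = 10% | f = 20% | f = 30% |
|---|---|---|---|---|
| 20% | 24% | 28% | 36% | 44% |
| 40% | 43% | 46% | 52% | 58% |
| 60% | 62% | 64% | 68% | 72% |

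The smallest excess is 0.05 × (1 − 0.60) = 2 points and the largest is 0.30 × (1 − 0.20) = 24 points.

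**What the right answer would be.** Some MOUD-only entrants do have OUD. Take p = 40% and f = 20%, and suppose half of the MOUD-only entrants are true cases. Uptake among true cases is then (0.80 × 0.40 + 0.10) / (0.80 + 0.10) = 0.42 / 0.90 = 46.7%. The plan would report 52%, which is 5.3 points high. A diagnosis-only denominator would report 40%, which is 6.7 points low.

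**Setting.** Suppose OTP setting has no real association with MOUD (odds ratio 1), p = 40%, and a share s of people in that setting are there only because of a MOUD code. Their MOUD probability is s + (1 − s) × 0.40, and the apparent odds ratio is the odds of that probability divided by 0.40/0.60.

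| s (assumed) | Probability | Apparent odds ratio |
|---|---|---|
| 10% | 0.46 | 1.28 |
| 30% | 0.58 | 2.07 |
| 50% | 0.70 | 3.50 |
| 80% | 0.88 | 11.0 |

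**Initiation.** The article does not define it, and a fuller plan may. A MOUD-free lookback alone would not remove the overlap: someone with a clean lookback whose entry code is a MOUD code still counts as an initiator, unless the entry claim itself is set aside.

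**The case against.** The strongest objection is that MOUD-only entrants may well have OUD. If they all do, they belong in the denominator, the cohort figure is right for identified patients, and dropping them would overstate the treatment gap. This stands in part. It means the diagnosis-only figure is not the truth either, and the 46.7% example shows error on both sides. It does not rescue a single all-entrant figure whose dependence on the entry rule is never shown.

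Four stronger readings are tempting, and the document does not support them.

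- *Two of the three routes are simply MOUD receipt.* Only the drug-code route is. The procedure route covers OUD-related services more widely, and treatment administration is one part of it.
- *The setting odds ratio is tautological, or the model separates.* MOUD services are part of the OTP definition, not all of it, and office-based MOUD falls under primary care, so MOUD recipients exist outside OTPs. The text also does not say how setting is assigned in this model, which an article may leave to a fuller plan.
- *The treatment gap is certainly understated.* The direction is certain relative to diagnosis-identified people. Relative to all people with OUD, it depends on how many MOUD-only entrants are true cases.
- *HIV testing and PrEP results are biased in the same way.* Their codes play no part in entry. Entrants without OUD could dilute them, but the document offers no basis for sizing this. It names no other uses of these drugs, and the code list (Table S1) is not shown. That list may drop some products, though a list alone cannot separate indications for a shared product.

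It is also fair that the model draws on literature and Aim 2 as well as Aim 1, and that every parameter is varied in one-way analyses. That tests dependence on the baseline but does not correct its central value.

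**Conclusion.** The point holds for MOUD receipt, and for MOUD initiation where the entry claim can count as the initiation. The drug-code route and the treatment-administration part of the procedure route use the codes that score the outcome. Uptake therefore exceeds that in diagnosis-identified people by f(1 − p). The direction of that comparison is certain. Its size is not, because the 2 to 24 points rest wholly on assumed f and p.

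The OTP setting is a partly circular covariate for MOUD initiation, with illustrative apparent odds ratios of 1.28 to 11.0 under assumed shares and no true association. Entry of some people without OUD is possible under the rule but cannot be sized. Retention is not circular in this way, since one fill does not give 180 days of cover.

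**What to change.** Keep the broad cohort for describing care use. For MOUD outcomes, change the following:

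1. Make the primary denominator for MOUD receipt and initiation the people identified by an OUD diagnosis code, independently of MOUD codes. For initiation, add a prespecified MOUD-free lookback.
2. Report the share of the cohort that entered by a MOUD code only.
3. Show the all-entrant estimate alongside as a sensitivity analysis. The two figures bracket the effect of the entry rule, and both should go to Aim 2 and to the agent-based model baseline.
4. In the MOUD initiation model, assign setting from the index OUD-diagnosis visit for everyone, whether or not they later start MOUD.

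Table 1 already lists the diagnosis codes, drug codes, and service and fill dates needed, so the cost is wording and code. The downside is a smaller denominator that omits some true OUD cases without a coded diagnosis and people already on MOUD when the data begin in 2012. Some overlap also remains where the index diagnosis is made at an OTP on the visit at which MOUD starts, so the number of such people should be reported.
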